**Neurofeedback als a treatment for MDD**

The intervention will consist of reducing AA in the prefrontal cortex with the use of NF. Participants will learn to increase elektrophysiological brain activity in the left prefrontal cortex in comparison to activity in their right prefrontal cortex. NF-sessions will take place in a maximum of 30 sessions three times each week. Every session will have a duration of 3x8 minutes separated by 4 minutes rest. Primary goal of the pilot-study is obtaining preliminary evidence about possible effectiviness of NF as a treatment for MDD. If at least 50% of the participants will respond (>50% reduction of symptomatology) at the end of treatment, this will considered as an indication of possible effectiveness. Further research in the context of a RCT will be carried out to establish efficacy.

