**Method**

*Design:*

10 Participants, meeting criteria for MMD according to DSM-IV-TR, will be recruited at the unit for treatment of mood disorders at the RIAGG Maastricht, and by advertisements in local media. Formal axis-1 diagnosis will be established with the SCID-1, a formal classification instrument for DSM-IV axis-1 disorders {First, 1995 #4782}. After signing informed consent, subjects will participate in the study.

*Inclusion criteria:*

- Primary axis-1 disorder of Major Depressive Disorder fulfilling DSM-IV criteria {APA, 1994 #87}.
- Written informed consent.

*Exclusion criteria:*

- History of brain trauma (commotio or constusio cerebri)
- Current use of antipsychotics, moodstabilizers or benzodiazepines. Current use of antidepressants is permitted if this medication is not changed within a period of 6 weeks prior to participation in the study. Additionally, no changes in antidepressant medication are allowed during active participation in the study.
- Chronic depression (> two years duration).
- Dysthymia as a primary axis-1 diagnosis
- Bipolar disorder as a primary axis-1 diagnosis
- Severe suicidality (HDRS item # 3 with a score >2) or severe depression symptomatology (HDRS score > 25).
- Pregnancy.
- Comorbid anxiety disorders and personality disorders are permitted.

*Outcome measures*

Main outcome measures are the Quick Inventory of Depressive Symptoms (QIDS-SR; {Rush, 2003 #2772}, the Hamilton Depression Rating Scale (HDRS; {Hamilton, 1967 #1598}, the Remission from Depression Questionnaire (RDQ; {Zimmerman, 2013 #5538} and change in AA between frontal cortical regions.

- The QIDS-SR is a 16-item self-rating scale to assess symptom severity of MDD and will be administered prior to each NF session (3 times a week).
- The HDRS is a 17-item clinician-rated scale for estimating severity of depression during the past week. It will be administered once a week by a trained research assistant during the 6-week study period.
- Before and after every NF session, participants will fill out the PANAS and the TEPS. The PANAS measures momentary positive and negative affects, the TEPS measures anhedonia. Goal of obtaining these instruments is to assess changes in emotions after each NF session.
- At baseline, demografic and medical information will be collected.

*Intervention:*

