After informed consent is obtained, the NF intervention will consist of maximum 30 sessions, each lasting 3 x 8 minutes divided by 2 breaks of 4 minutes. Prior to and after each session, baseline EEG alpha-activity will be measured at right- and left frontal regions. Sessions will be done 3 times a week. If after 30 sessions no improvement in clinical condition has occurred, we will offer participants an evidence-based treatment in our outpatient mental health center (RIAGG Maastricht) or the outpatient facility of the department of psychiatry at the Maastricht University Hospital. Additionally, the NF treatment will be stopped in cases of severe suicidality or severe depression symptomatology ( QIDS-SR score > 21). In these cases, the research assistant will contact the principal investigators who will responsible for referral for standard depression treatment.

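### A full course of 30 sessions at three per week takes 10 weeks, but the weekly HDRS and the study duration are set at 6 weeks, so sessions 19 to 30 have no scheduled HDRS.

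*Protocol*

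**What the plan says.** **Length of treatment.** The section on neurofeedback as a treatment for MDD states: "NF-sessions will take place in a maximum of 30 sessions three times each week". Method, Intervention repeats the maximum of 30 and adds: "Sessions will be done 3 times a week". It also says what is offered to participants who have not improved after 30 sessions, so a full course is foreseen.

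**HDRS schedule.** Method, Outcome measures lists the HDRS among the main outcomes and says: "It will be administered once a week by a trained research assistant during the 6-week study period". It describes the scale as covering the past week. Ethical issues separately limits the study to 6 weeks.

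**QIDS-SR schedule.** The same outcome list says that the QIDS-SR "will be administered prior to each NF session (3 times a week").

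**Severity limits.** At entry, the exclusion criteria name: "Severe suicidality (HDRS item # 3 with a score >2) or severe depression symptomatology (HDRS score > 25"). During treatment, the Intervention text says: "the NF treatment will be stopped in cases of severe suicidality or severe depression symptomatology ( QIDS-SR score > 21"). In those cases "the research assistant will contact the principal investigators", who arrange referral.

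**Success criterion.** The pilot is judged on this condition: "If at least 50% of the participants will respond (>50% reduction of symptomatology) at the end of treatment". No scale is named for it.

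**The concern.** The session count and frequency do not fit the stated study period, so a site cannot follow both. If the sessions are delivered as written, the HDRS schedule ends before treatment does. Two things are then at stake.

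- **Outcome.** A clinician-rated main outcome has no scheduled value at the time point where the pilot is judged.
- **Safety.** The treatment stop uses the term severe suicidality, and the protocol defines that term only through HDRS item 3. In the last weeks of a full course that item is not scheduled. The participants still in treatment at session 30 include those who have not improved.

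**Working it through.** **Inputs**

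| Input | Value | Place in protocol |
|---|---|---|
| Maximum sessions | 30 | Neurofeedback as a treatment; Method, Intervention |
| Frequency | 3 per week | same two places |
| HDRS | weekly, 6 weeks | Method, Outcome measures |
| Study duration | at most 6 weeks | Ethical issues |
| Participants | 10 | Method, Design |

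**Step 1. Can the stated 6 weeks be reproduced?** Weeks = sessions / sessions per week = 30 / 3 = 10. It cannot. Fitting 30 sessions into 6 weeks would need 30 / 6 = 5 per week, against 3 stated.

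**Step 2. Sessions inside the HDRS schedule.** 6 weeks × 3 = 18. Sessions outside it: 30 − 18 = 12, that is sessions 19 to 30, in weeks 7 to 10. Share: 12 / 30 = 40%. A rating late in week 6 could fall just before session 19, which moves the boundary by about one session at most.

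**Step 3. Distance from the last HDRS to the end of treatment.** 10 − 6 = 4 weeks. Because the scale looks back one week, a week-6 rating says nothing about weeks 7 to 10.

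**Step 4. Ratings needed to close the gap.** 10 − 6 = 4 per participant. For 10 participants: 4 × 10 = 40 at most.

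**Step 5. The suicidality stop.** The entry criterion attaches a measure to each of two terms: item 3 > 2 for suicidality and total HDRS > 25 for depression severity. The stop uses the same two terms and prints one measure, QIDS-SR > 21, next to depression severity. There are three ways to read the suicidality part:

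- It takes the entry definition. Then the defining rating is not scheduled in weeks 7 to 10.
- It rests on clinical judgement. Then it works at any session but has no operational definition.
- The QIDS-SR limit covers both terms. Then a total score stands in for suicidality, which it does not isolate.

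The text does not say which is meant, and each reading needs a wording change.

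**The case against.** **The 6-week limit may not belong to this design.** Ethical issues speaks of sham treatment, of a code for active or sham allocation, and of a duration derived from a pilot study, while this protocol is itself the pilot. The limit looks carried over from a sham-controlled trial, although the document cannot prove that. This stands, and it bears on the remedy: 10 weeks is the natural correction. It does not remove the contradiction, because the outcome section states the 6-week period separately for the HDRS.

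**Thirty is only a maximum.** True, and a course of 18 sessions or fewer has no gap. But the protocol plans explicitly for participants who reach session 30.

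**A reader might infer that participants are unmonitored for suicidality in weeks 7 to 10.** The documents do not support this. The QIDS-SR precedes every session, audio contact and video surveillance run during sessions, participants may leave at any moment, and severe suicidality that becomes known at any session stops treatment. Only the scheduled item 3 rating lapses.

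**A reader might also count it as an error that an on-study HDRS above 25 triggers no action.** Entry and stop limits need not match, and stopping on a measure taken three times a week is a coherent choice. How often HDRS exceeds 25 with QIDS-SR at 21 or below cannot be computed from the document. A review trigger there is optional. So is a QIDS-SR check at screening, since the rating before session 1 already identifies anyone above 21.

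**Conclusion.** The contradiction is certain from the text: 10 weeks of sessions against a 6-week HDRS schedule and a 6-week study. In a full course at the stated frequency, 12 of 30 sessions (40%) have no scheduled HDRS, and the last rating falls 4 weeks before the end of treatment.

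Two consequences carry conditions. The effect on the response criterion applies only if the HDRS is the scale used, because none is named. The effect on the suicidality stop applies only if the entry definition, item 3 > 2, is meant to govern on study, which is an inference. If 6 weeks governs instead, the gap closes, but the 30-session text is then wrong. The point should be fixed before use. It is a scheduling and wording error and does not show that safety monitoring is absent.

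**What to change.** 1. Change the 6-week statements in Method, Outcome measures and in Ethical issues to 10 weeks.
2. Continue the weekly HDRS until the last session, and add an explicit end-of-treatment rating for participants who finish at any point.
3. State in Method, Intervention that HDRS item 3 > 2 triggers the severe-suicidality stop. Keep QIDS-SR > 21 as the per-session stop for depression severity.

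**Cost.** Wording, at most 4 extra weekly ratings per participant (40 in total) by the existing research assistant, and a stated burden that is 4 weeks longer. Ethical issues justifies the burden by the 6-week limit, so that argument must be rewritten.

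Keeping 6 weeks and capping treatment at 18 sessions would also be consistent and needs no extra ratings. It gives up 12 of the 30 possible sessions to preserve a duration of doubtful origin, so it is the weaker choice.

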**Procedure**

After signing informed consent, participants will be invited to the neurofeedback laboratory of the school for Mental Health and Neuroscience (MheNS). This laboratory is a facility that meets the requirements as outlined in NEN 60601 by the Nederlands Normalisatie-instituut. The intervention will take place while participants sit behind a table and look at a monitor on top of this table. The monitor displays a visual feedback signal (thermometer) based on real-time analysis of their elektrophysiologidal data. The participants are instructed to raise the bar of the thermometer (which is indicative of a decrease in AA). During the NF sessions, while being in the laboratory, participants are in constant contact with the research assistant through an audio-channel, additionally there is constant video-surveillance. Prior to the NF session, depression-severity will be assessed as outlined above (see outcome measurements).

EEG-elektrodes will be attached following the international 10-20 system at F3, F4, C3, C4, P3 en P4. EEG will be referenced by 2 elektrodes attached to the earlobes. Under and above the left eye an elektrode will be placed to measure EOG. The elektrode will be applied after cleaning the skin with scrubgel. The impedance on all locations will be kept lower than 5 KΩ.

At the start of each NF session, the baseline EEG is being measures without NF to assess baseline AA which serves as a starting point for feedback. Measuring baseline prior to each session is necessary as can be expected that, at least in the active arm, AA decreases over time. Data collection will be channeled through an acquisition PC with a BrainAmp DC EEG amplifier (Brain Products) using a 1000 Hz sample frequency. Online calculations are done by a filter written for BrainVision RecView. The data will be epoched online into 2.048-s epochs that overlap by 75% and then transformed by a fast Fourier transform (FFT) to the frequency domain (frequency resolution 0.488 Hz). Every 0.512 second, the power within the alpha frequency band (7.8 Hz – 13.1 Hz) of both F3 and F4 will be calculated. AA is computed as the difference of the natural log-transformed F3 and F4-alpha power: Ln(F3-alpha) – Ln(F4-Alpha). Current asymmetry is subsequently compared to the personal mean baseline asymmetry. The result of the calculation will be sent to a stimulus PC running Presentation stimulus delivery software (Neurobehavioral Systems) with an 8-bit parallel port (LPT-port) to control a paradigm showing a visual representation of the asymmetry. In the Presentation paradigm, the last 20 values of the asymmetry are used in a moving average to prevent ‘jitter’ in the feedback. Participants receive feedback with visual feedback; they are instructed to increase the level of a thermometer that is shown on a flatscreen. Additionally, a numerical score below the thermometer indicates their actual total performance. This score is adjusted (i.e. increased) continuously by a number ranging from 0 and 128, depending on the level of the thermometer. In this way a good actual performance (a shift in asymmetry in the desired direction) results in an increasing total score. A big shift in the desired direction results in a rapidly increasing total score, whereas a small shift in the desired direction results in a slow increasing total score. A shift in the undesired direction produced no change in total score. The purpose of this total performance score is to give participants feedback on the differential effect of the sessions.

# **Ethical issues**

Participants will be receive written and verbal information about the procedure and have the right to discontinue participation at any moment. Partcipants wil receive either an experimental or sham experimental treatment for their depressive disorder. To minimize burden resulting from participation in the study, the duration of the study is kept to a maximum of 6 weeks. This duration is based on data from our pilot-study and is totally comparable to the duration of RCT’s that examine novel antidepressants with the use of placebo. Given the extensive waiting-lists for regular evidence-based treatments for depression (3-4 months), participation in the study does not lead to additional delay in the start of standard therapy. Thus, those participants that wish to receive standard antidepressant treatment after participation in the study, will receive such treatment within a normal time-frame.

As mentioned earlier, no side-effects of NF are reported in the literature. Moreover, in our pilot-study in depressed participants, we did not observe any side-effects.

There will be an independent physician available to address all questions and concerns of potential participants. All participants will provide written informed consent. Their data will be collected in a anonymized in a central database in our laboratory. Participants can withdraw consent at any moment without any restrictions. If requested, all participants can be informed of the final results after completion of the study.

All data will be coded and stored anonymously. Each participant will be assigned to an unique code. Access to data and code are restricted to research assistants and principal investigators. The code that entails information about active or sham-treatment will be opened after completion of the study.

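### The Protocol describes both a one-group neurofeedback pilot and a sham-controlled masked study, so its 50% success rule has no settled meaning

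*Protocol*

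**What the plan says.** **One group.** The section Neurofeedback als a treatment for MDD gives the aim: "Primary goal of the pilot-study is obtaining preliminary evidence about possible effectiviness of NF as a treatment for MDD". It sets the success rule: "If at least 50% of the participants will respond (>50% reduction of symptomatology) at the end of treatment", this counts as an indication of possible effectiveness. It then places the controlled trial in the future: "Further research in the context of a RCT will be carried out to establish efficacy". The Hypothesis section states an association between neurofeedback and symptom reduction and names no comparator. Under Method, the design paragraph says "10 Participants, meeting criteria for MMD according to DSM-IV-TR, will be recruited" and mentions no arms, allocation or masking. The Intervention text describes neurofeedback only.

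**Two groups.** The Procedure section explains why baseline EEG is repeated by an expectation that "at least in the active arm, AA decreases over time". Ethical issues says "Partcipants wil receive either an experimental or sham experimental treatment for their depressive disorder", and later "The code that entails information about active or sham-treatment will be opened after completion of the study".

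**An earlier pilot.** Ethical issues also bases the study duration on data from the team's own pilot, and reports that "in our pilot-study in depressed participants, we did not observe any side-effects". The only pilot that the Protocol describes is the present study.

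**The concern.** Whether a sham arm exists is a basic design fact, and the Protocol gives both answers. Three separate statements in two sections point to two arms, so this is not a single slip of wording. Nothing in the document reconciles them.

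The only stated success criterion depends on the answer. It counts responders among all participants. If everyone receives neurofeedback, that share is at least a response rate on neurofeedback. If some receive sham, it is an average over two treatments, and sham responders count as evidence for neurofeedback. If there is no sham, the ethics text gives a wrong account of what participants receive and suggests a masked comparison that the study does not contain.

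**Working it through.** **Inputs from the Protocol.** Sample size is 10 (Method). The rule is at least 50% responding (Neurofeedback als a treatment for MDD), that is 0.50 × 10 = 5 or more responders. The Protocol states no error rate, power, assumed response rate or allocation ratio, so there is no further figure to reproduce.

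**Assumptions.** Response on active is 50%, the rule's own threshold. Under the two-arm reading the split is 5 active and 5 sham. Sham response q is varied from 10% to 40%.

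**Reading 1: all 10 on neurofeedback.** With X ~ Bin(10, 0.5), P(X ≥ 5) = 1 − (1 + 10 + 45 + 120 + 210)/1024 = 638/1024 = 0.62.

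**Reading 2: 5 active, 5 sham, rule pooled as written.** With A ~ Bin(5, 0.5) and S ~ Bin(5, q),

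P(A + S ≥ 5) = Σ P(S = s) × P(A ≥ 5 − s), for s = 0 to 5.

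The values of P(A ≥ 5 − s) for s = 0, 1, 2, 3, 4, 5 are 1/32, 6/32, 16/32, 26/32, 31/32 and 1.

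For q = 0.10: 0.5905 × 0.0313 + 0.3281 × 0.1875 + 0.0729 × 0.5 + 0.0081 × 0.8125 + smaller terms = 0.12.

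| Sham response q | Expected pooled rate (0.5 + q)/2 | P(rule met) |
|---|---|---|
| 10% | 30% | 0.12 |
| 20% | 35% | 0.24 |
| 30% | 40% | 0.36 |
| 40% | 45% | 0.50 |

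**Sensitivity to the active rate.** With 60% on active, the rule is met with probability 0.83 if all 10 are active, and 0.50 if 5 are on sham with 30% response.

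**What the pooled rule can hide.** With the same 5:5 split, 2 of 5 active responders plus 3 of 5 sham responders gives 5/10. The rule is met although sham did better (60% against 40%). Conversely, 4 of 5 active and 0 of 5 sham gives 4/10. The rule fails although 80% of active participants responded.

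**Reading 2 with the rule on the active arm only.** At least 50% of 5 means 3 or more. P(A ≥ 3) = 16/32 = 0.50 at a true response of 50%, and 0.16 at 30%.

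**The case against.** The best case for the Protocol is that the aim, hypothesis, design, intervention and success rule all support one group. Under that reading the 50% rule is coherent, the randomised trial is plainly deferred, and the remedy is to remove stray wording. That stands, and it makes the single-arm reading the more likely one. It remains an inference, because the Protocol never calls itself single-arm or open-label, and the ethics text says outright that sham is given. A statistical analysis plan could supply a between-arm comparison, so the absence of one is not held against the Protocol here. It could not decide which of two contradictory Protocol statements about treatment is true.

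The probabilities rest on an assumed split and assumed response rates. That also stands. They show how far the rule's meaning moves between readings and do not predict this study's result.

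Several stronger readings are tempting, and the document does not support them:

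- A reader might infer that participants are told of a sham they cannot receive, which would alter their expectations. The consent text is not shown, and Ethical issues is not participant information.
- A reader might infer that the cited pilot is certainly this study, so that the duration and safety statements rest on data not yet collected. The past-tense report of no side-effects leaves room for a separate earlier pilot. The safety statement also cites the literature first.
- A reader might conclude that the two-arm wording was carried over from a controlled-trial protocol. That is plausible but not provable, and the point does not need it.
- A reader might add that no side-effect recording is planned. That is a separate question, to be judged beside the repeated questionnaires, stopping criteria and session surveillance. It has no bearing on whether there are one or two arms.

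**Conclusion.** The contradiction is real and should be resolved before the study is run or reported. One of the two descriptions is wrong as written.

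If a sham arm is run, the success rule as worded does not measure neurofeedback. With an assumed 5:5 split and 50% response on active, the chance of meeting it is 0.12 to 0.50 for sham response of 10% to 40%, against 0.62 with all 10 on neurofeedback. If no sham arm is run, the rule can stand as a one-group criterion, but Ethical issues misstates the treatment and implies masking.

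The contradiction itself rests on no assumption; only its numerical size does. The reference to the team's own pilot is ambiguous and needs identifying. It is not shown to be false.

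**What to change.** State one design in Method and align every section with it.

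- **If single-arm**, which the aim, hypothesis, design and intervention text support: delete the active-arm phrase from Procedure and the sham and code-opening sentences from Ethical issues. State that the study is open-label and uncontrolled. The 50% rule can then stay as worded.
- **If a sham arm is intended**: state the allocation, the sham procedure and who is masked, and apply the 50% rule to the active arm only. The sponsor should accept knowingly that, with 5 active participants, this rule passes only half the time at a true 50% response.

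Under either choice, check that the participant information matches the chosen design. Say which pilot Ethical issues refers to. If it is a separate completed study, identify it. If it is the present study, remove the duration and side-effect statements that rest on it.

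The single-arm route costs only Protocol wording and a check of the participant information. The sham route also needs a sham and a masking procedure to be written, and leaves fewer participants on neurofeedback out of the 10.
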